# Intramuscular oxytocin versus oxytocin/ergometrine versus carbetocin for prevention of primary postpartum haemorrhage after vaginal birth: study protocol for a randomised controlled trial (the IMox study)

**DOI:** 10.1186/s13063-018-3109-2

**Published:** 2019-01-03

**Keywords:** Postpartum haemorrhage, Prevention, Primary, Oxytocin, Oxytocin/ergometrine, Carbetocin

## Abstract

**Background:**

Postpartum haemorrhage remains a major cause of maternal mortality and morbidity worldwide. Active management of the third stage of labour reduces the risk of postpartum haemorrhage. Oxytocin and oxytocin/ergometrine are commonly used in the UK, with oxytocin/ergometrine being more effective at preventing moderate, but not severe, blood loss. Many guidelines specifically recommend using oxytocin for all vaginal births, as it is associated with fewer adverse events. However, a survey conducted by the Southmead Hospital Maternity Research Team revealed that 71.4% of UK obstetric units still routinely use oxytocin/ergometrine. Carbetocin is a newer medication that may be as effective but has fewer side effects. No studies have directly compared all three medications.

**Methods:**

The IMox study aims to determine the most effective, acceptable and cost-effective drug for primary prevention of postpartum haemorrhage following vaginal birth. The IMox study is a prospective, multi-centre, double-blind, randomised trial directly comparing oxytocin, oxytocin/ergometrine and carbetocin given intramuscularly for the prevention of postpartum haemorrhage in the third stage of labour. The primary effectiveness outcome is the use of an additional uterotonic drug. Secondary effectiveness outcomes reflect maternal morbidity and mortality within the immediate postpartum period. Participant questionnaires and subjective reporting of side effects will be used to evaluate maternal acceptability. Maternal quality of life utilities will be collected antenatally, and on days 1 and 14 after birth to enable a cost-effectiveness assessment of each studied drug.

Participants will be pregnant women planning a vaginal birth in six hospitals in England. Participants will be approached and invited to provide consent to participate from 20 weeks gestation until in established labour. A complete sample of 5712 participants (1904 per arm) providing data for the primary outcome will allow for a robust determination of efficacy between all three study drugs. Data will be collected until participants are discharged from the hospital and on postnatal days 1 and 14 regardless of location. All analyses will be on a modified intention-to-treat basis, and additionally repeated on a per protocol basis. Data collection commenced in Feburary 2015 and was completed in August 2018.

**Discussion:**

This study is the first to directly compare oxytocin, oxytocin/ergometrine and carbetocin in the same population for the prevention of postpartum haemorrhage following vaginal birth. Furthermore, this study will be the first to directly compute health economic outcomes from such a three-way comparison. This study is limited to using short-term outcomes, and so will not provide evidence for important outcomes such as long-term maternal psychological well-being and time to next conception.

**Trial registration:**

ClinicalTrials.gov, NCT02216383. Registered on 18 August 2014. EudraCT, 2014-001948-37. Registered on 23 September 2014. ISRCTN, ISRCTN10232550. Retrospectively registered on 6 March 2018).

**Electronic supplementary material:**

The online version of this article (10.1186/s13063-018-3109-2) contains supplementary material, which is available to authorized users.

## Background

Primary postpartum haemorrhage (PPH), defined as a loss of ≥500 ml of blood from the genital tract within 24 h of delivery, remains a major cause of maternal morbidity and mortality worldwide, accounting for more than a quarter of all global maternal deaths [1]. In addition to the significant risk of immediate adverse events, PPH is significantly associated with long-term physical and psychological morbidity [2]. The need for treatments such as additional uterotonic drugs, blood transfusion, operative procedures including hysterectomy and prolonged hospital stay affect not just the woman experiencing the haemorrhage, but also her family and the health service, which incurs additional costs. Approximately 70% of PPHs are caused by inadequate uterine contraction after delivery of the placenta (uterine atony) [3]. Prophylactic administration of a uterotonic drug in the third stage of labour, together with early cord clamping and controlled cord traction, reduces the incidence of primary PPH by 66%, when compared with physiological management [4]. The majority of women who experience PPH have no risk factors [5], and it is therefore recommended that this active management of the third stage of labour (AMTSL) is routinely offered to all labouring women [5–7].

There are several prophylactic uterotonic agents available for use, including oxytocin, oxytocin/ergometrine and carbetocin. Oxytocin and oxytocin/ergometrine are commonly used for vaginal deliveries, while carbetocin is presently only licensed for use at caesarean section. Carbetocin is a synthetic analogue of oxytocin which provides a longer duration of action than oxytocin (half-life 85–100 min versus 3–4 min) [8].

Although there are no trials directly comparing all three of oxytocin, oxytocin/ergometrine and carbetocin for prophylaxis of PPH after vaginal birth, a Cochrane network meta-analysis (NMA) on this subject was published in 2018 [9]. This NMA demonstrated rates for PPH ≥ 500 ml of 10.5%, 7.2% and 7.6% for oxytocin, oxytocin/ergometrine and carbetocin respectively, and rates of PPH ≥ 1000 ml of 3.6%, 2.8% and 2.5% respectively. Additionally, the NMA demonstrated higher rates of adverse outcomes following the use of oxytocin/ergometrine than both oxytocin and carbetocin (hypertension 1.2%, 0.7% and 0.6% respectively and vomiting 1.9%, 0.5% and 0.6% respectively).

Since publication of this NMA, the results of a large multi-national non-inferiority clinical trial in 30,000 women of oxytocin versus carbetocin for prophylaxis of PPH have been published by Widmer et al. [10]. This trial demonstrated non-inferiority of carbetocin relative to oxytocin for the prevention of PPH ≥ 500 ml (relative risk (RR) 1.01; 95% confidence interval (CI), 0.95 to 1.06). The use of additional uterotonic agents and interventions to stop bleeding and the occurrence of adverse effects were not shown to differ significantly between the two groups.

The trial was not sufficiently powered to demonstrate non-inferiority for PPH ≥ 1000 ml.

Taken together, these recent results suggest that carbetocin may be as effective as (or potentially more effective than) oxytocin, and associated with fewer adverse events than oxytocin/ergometrine.

Current national and international guidelines advocate the use of intramuscular oxytocin as the prophylactic uterotonic agent of choice in the third stage of labour for low-risk women delivering vaginally [5–7, 11]. However, an unpublished telephone survey of all obstetric units in the UK in October 2013 conducted by our team found that 71% of units still use oxytocin/ergometrine for normotensive women having a vaginal birth despite these recommendations. Many units volunteered that their local departmental audits had shown increases in their PPH rates following a switch to oxytocin in line with national guidance, and that they therefore reverted to oxytocin/ergometrine despite its known side effects. The care being provided to women on a national scale is clearly suboptimal in this respect, which suggests that an alternative prophylactic uterotonic agent may be needed.

Very few studies have investigated the cost-effectiveness of carbetocin. The need for new studies investigating the cost and cost consequences of carbetocin was highlighted in a Cochrane review [12]. This additional information is crucial, particularly as carbetocin is more expensive at UK list price (£17.64 versus £0.91 for oxytocin and £1.38 oxytocin/ergometrine), and any additional benefits or resource use would need to be weighed against the higher acquisition price.

While the recent Cochrane NMA and the study by Widmer et al. add substantial weight to the case that carbetocin may be as effective as (and potentially more effective than) oxytocin and associated with fewer adverse events than oxytocin/ergometrine, the resistance to bring practice into line with current guidelines (at least within the UK) demonstrates the need for primary direct trial evidence for the clinical effectiveness, maternal acceptability and cost-effectiveness of these commonly used drugs.

## Methods/design

### Aims

The primary study aims are to determine if:Carbetocin is at least as effective as oxytocin/ergometrineCarbetocin is more effective than oxytocinOxytocin/ergometrine is more effective than oxytocin

The secondary study aims are to establish whether:Carbetocin is associated with fewer adverse events than oxytocin/ergometrine and oxytocinCarbetocin is a cost-effective alternative to oxytocin/ergometrine and oxytocin

### Trial design and justification of comparisons

The IMox study is a multi-centre, double-blinded, randomised trial to compare oxytocin, oxytocin/ergometrine and carbetocin given intramuscularly after vaginal birth for prevention of primary PPH. Drugs will be compared in terms of clinical effectiveness, maternal acceptability and cost. Participants will be randomised to parallel arms in a 1:1:1 ratio. A Consolidated Standards of Reporting Trials (CONSORT) diagram of the IMox study is given in Fig. 1.

**Fig. 1 Fig1:**
[figure not shown]
CONSORT diagram of the IMox study

A non-inferiority comparison between carbetocin and oxytocin/ergometrine has been chosen, as oxytocin/ergometrine is associated with greater maternal side effects. Should carbetocin be non-inferior to oxytocin/ergometrine for the primary outcome and be associated with fewer maternal side effects, it is likely to be superior as a prophylactic uterotonic drug. Superiority comparisons will be drawn between oxytocin/ergometrine and oxytocin as well as carbetocin and oxytocin.

### Participants

Women aged ≥ 18 years with a live singleton pregnancy who have a vaginal birth (spontaneous or instrumentally assisted) at any gestation are eligible to participate. The exclusion criteria are as follows: women with known or suspected antenatal hypertensive disorders, intrapartum hypertension (defined as a single systolic blood pressure ≥ 160 mmHg, or two consecutive blood pressures of ≥ 140 mmHg systolic or ≥ 90 mmHg diastolic taken 30 min apart), antepartum haemorrhage of ≥ 50 ml, confirmed maternal coagulation disorder or intrauterine fetal death in the current pregnancy, women who would decline blood products, women with severe peripheral vascular, cardiac or hepatic disease, women with epilepsy, women with an allergy or sensitivity to any of the ingredients in any of the study drugs, women unable to read and write English sufficiently as to preclude completion of maternal questionnaires and caesarean section.

### Setting

The sites will be six maternity units across the south-west and centre of England. These include teaching hospitals and district general hospitals.

### Intervention

A single dose intramuscular injection of the study drug (10 IU oxytocin or 500 μg/5 IU oxytocin/ergometrine or 100 μg carbetocin) will be given immediately after the vaginal birth of the baby and clamping of the umbilical cord.

### Outcomes

#### Primary clinical outcome

The primary outcome measure is the proportion of women requiring additional uterotonic drugs after administration of the study drug. This primary outcome measure was chosen over severity of PPH for the following reasons: estimation of obstetric blood loss is known to be inaccurate regardless of the mode of estimation [13, 14]; vaginal or cervical tears contribute to the incidence and severity of PPH without any role of uterine atony; lastly the administration of several additional uterotonic drugs may in some cases be used to successfully avoid blood loss of ≥ 500 ml. This would not be captured with a primary outcome of PPH incidence, which would not account for the clinically important (and costly) administration of additional uterotonics.

#### Secondary outcomes

##### Secondary effectiveness outcomes

Secondary effectiveness outcomes will include the number and type of additional uterotonic drugs required, weighed estimated blood loss at delivery (in millilitres), transfusion of blood products (number of units and type of blood product), use of other surgical/mechanical measures to treat PPH (need for manual removal of the placenta/examination under anaesthetic/intrauterine balloon/uterine compression suture/interventional radiology/hysterectomy) and maternal blood pressure at 1 and 2 h postnatal.

##### Maternal acceptability outcomes

Patient-reported outcomes will include symptoms of nausea, vomiting, headache, dizziness or abdominal pain.

##### Other data collected and cost outcomes

Other data collected to allow for adjustment of results and analysis are maternal age, body mass index (BMI), ethnicity, history of past PPH, gravity, parity, onset of labour (spontaneous or induced), length of first, second and third stages of labour (in minutes), intrapartum pyrexia, weight of baby, mode of birth, gestation at birth, length of inpatient stay, use of oxytocin to induce or augment labour, use of terbutaline sulphate during labour, use of tranexamic acid, length of time spent in recovery (minutes), length of time between delivery and discharge from the labour ward (minutes), total length of the postnatal hospital stay (minutes) and maternal health-related quality of life (measured with the EQ-5D-5 L antenatally, day 1 and day 14 postpartum).

### Patient and public involvement

Patients and the public were not involved with the design, planning or delivery of the IMox study. Results of the study will not be directly communicated to study participants due to the considerable burden of doing so. However, summaries of results will be distributed using existing networks of patients (such as Maternity Voices, a maternity advocacy group within the South West of England).

### Recruitment

Eligible women will be approached by members of the research team in the study sites from 20 weeks gestation. Each woman will be provided with a Participant Information Leaflet (PIL) and invited to provide her informed consent. No trial procedures will take place before informed consent is received.

### Blinding, randomisation and allocation

Participants, members of the research team and clinical staff caring for the woman will be blinded to the allocated uterotonic. Study drugs will be manufactured in identical 1-ml vials by an independent pharmaceutical unit and block-randomised according to a computer-generated randomisation code. When vaginal birth is imminent, the next consecutively numbered study drug will be taken from the labour ward refrigerator and administered. Unblinding will be possible in emergency clinical situations where knowledge of the administered drug would change the patient’s management via a 24-h telephone service.

### Data collection methods

Primary and secondary outcome data will be collected before the participant is discharged from the labour ward. Maternal quality of life data will be collected in person antenatally prior to the onset of labour and on day 1 postnatally during an interview with a member of the study team. Maternal quality of life at 2 weeks postpartum will be collected via a telephone interview with the participant. If participants are not contactable by telephone, they will be sent a data collection form with a stamped, addressed envelope. A participant timeline is shown in Fig. 2. All data will be entered into an online, password protected Microsoft Access database (Microsoft Corporation, Redmond, Washington, USA) by members of the research team. The structure of the IMox study is shown in (Fig. 3).

**Fig. 2 Fig2:**
[figure not shown]
Participant timeline for the IMox study

**Fig. 3 Fig3:**
[figure not shown]
SPIRIT diagram for the IMox study

### Sample size

The sample size selected for use in this study is 5712 participants returning data for the primary outcome. This sample size is large enough to cover all three comparisons. A drop-out rate of less than 0.5% between randomisation (birth imminent) and administration of drug is anticipated; therefore, the sample size has not been inflated.

We are investigating whether carbetocin is at least as effective as oxytocin/ergometrine and more effective than oxytocin, based on a primary outcome measure of the need for additional uterotonic drugs. Limited previous research indicates that carbetocin may be more effective than oxytocin/ergometrine at preventing PPH and is associated with significantly fewer side effects. Therefore, if carbetocin is robustly shown to be non-inferior to oxytocin/ergometrine for the primary outcome and is associated with fewer maternal side effects, it would be more appropriate for use as a prophylactic uterotonic drug.

Comparisons made will therefore be:Superiority comparison between oxytocin/ergometrine and oxytocinSuperiority comparison between carbetocin and oxytocinNon-inferiority comparison between carbetocin and oxytocin/ergometrine

The study will be powered in accordance with European Medicines Agency guidelines and with caution exercised on the available historical data.

Broadly pooled weighted mean prevalence (weighted for study size) data on the need for additional uterotonic drugs, from the published literature comparing intramuscular uterotonics for vaginal deliveries, are shown in Table 1. Therefore, the differences between drugs equate to approximately 4 points.

**Table 1 Tab1:** Prevalence of primary outcome by uterotonic drug in the published literature

	Pooled prevalence: need for subsequent additional uterotonic drugs	Percentage not requiring additional uterotonic drugs
Oxytocin	19.1%	80.9
Oxytocin/ergometrine	15.2%	84.8
Carbetocin	11.5%	88.5%

Adapted from [12, 23]

#### Superiority comparisons

To identify a 4-point difference (equivalent to a 20% reduction (15/19 = 0.8), which is clinically significant) between the current nationally recommended drug (oxytocin) and the current most commonly used drug (oxytocin/ergometrine), a sample size of 1904 per arm would provide at least 88% power for this comparison with an α of 0.05. The comparison would have a power of 80% for a Bonferroni-corrected level of nominal significance of α = 0.0167.

To identify an 8-point difference (equivalent to a 40% reduction (11/19 = 0.6), which is clinically significant) between the current nationally recommended drug (oxytocin) and the new alternative (carbetocin), the proposed sample size of 1904 per arm would have at least 99% power for this comparison either using an α of 0.05 (two-sided) or with a Bonferroni-corrected α of 0.0167.

#### Non-inferiority comparison

Non-inferiority is assessed using a two-sided CI for the difference in proportions, and significance declared should the CI lie entirely on the correct side of the non-inferiority margin. For a two-sided 95% CI, a sample size of 1904 per arm has 95% power for a non-inferiority margin of 1% using the estimated prevalence data. A Bonferroni-adjusted approach, using a two-sided 98% CI would have a power of 88% under the same scenario.

Based on the above, and in acknowledgement that the historic prevalence data may be not be precise, the trial will proceed on a target sample size of *n* = 1904 per arm. In accordance with the European Medicines Agency Guideline on Multiplicity Issues in Clinical Trials [15], an α = 0.05 will be used to determine statistical significance for all three contrasts, and additionally a threshold of α = 0.0167 (i.e. Bonferroni-corrected levels of significance) will be used for definitive statistical evidence.

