The chi-square test of association for a two by two cross-tabulation (equivalent to a test for a difference in two binomial proportions) will be used to examine superiority between oxytocin/ergometrine and oxytocin and between carbetocin and oxytocin. These differences will be further summarised using 95% Wald CIs for the difference between two independent proportions along with 95% CIs for the odds ratio and relative risk. Statistical significance will be declared if effects are in the anticipated direction and if the two-sided *p* value is less than 0.05. Definitive statistical significance will be declared if the *p* value is below 0.0167 (Bonferroni-adjusted level of significance). The non-inferiority comparison between carbetocin and oxytocin/ergometrine will proceed using a two-sided 95% CI for the percentage in need of additional uterotonic drugs. Non-inferiority will be declared if this interval excludes the non-inferiority margin.

Multivariable logistic regression for the primary outcome variable will also be used to adjust for known PPH risk factors: previous PPH, Asian ethnicity, obesity (BMI ≥ 35), induction of labour, operative vaginal birth, prolonged labour (≥ 12 h), big baby (≥; 4 kg), pyrexia in labour (≥ 38 °C once or ≥ 37.5 °C twice 2 h apart) and parity [5]. We will also control for clustering by centre by adjusting for maternity units as fixed effects. A PPH risk factor will only be included in the model providing missing data is less than 20%. Multiple imputation will be used to examine sensitivity of conclusions to missing data on PPH risk factors.

Analyses for all secondary outcomes and subsequent analyses will be superiority analyses. Analyses for secondary outcomes will comprise an omnibus test (parametric analysis of variance (ANOVA), Kruskal-Wallis test, chi-square test of association as appropriate) and appropriate pairwise comparisons between trial arms. Regression models will also be used to adjust for PPH risk factors. These models will be multivariable logistic regression models for binary outcomes and multivariable linear regression models (with appropriate transformation of the outcome if required) for scale outcomes.

Effect sizes and their associated 95% CIs will be calculated for each pairwise comparison.

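### The definitive (0.0167) tier is not carried into the non-inferiority decision rule, and its interval is printed as 98% where 0.05/3 gives 98.33%

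*Protocol article*

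**What the plan says.** The article names three primary contrasts: two superiority comparisons against oxytocin, and one non-inferiority comparison of carbetocin with oxytocin/ergometrine.

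The Non-inferiority comparison subsection of Sample size assesses non-inferiority with a two-sided interval for the difference in proportions. It says that 1904 per arm with a 95% interval "has 95% power for a non-inferiority margin of 1% using the estimated prevalence data". It continues: "A Bonferroni-adjusted approach, using a two-sided 98% CI would have a power of 88% under the same scenario".

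The next paragraph of that subsection fixes the levels. First, "an α = 0.05 will be used to determine statistical significance for all three contrasts". In addition, "a threshold of α = 0.0167 (i.e. Bonferroni-corrected levels of significance) will be used for definitive statistical evidence". The Superiority comparisons subsection uses 0.0167 as well.

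The data analysis section on drug efficacy gives both tiers for the superiority tests: significance at a two-sided p value below 0.05, definitive significance below 0.0167. For the remaining contrast it says: "The non-inferiority comparison between carbetocin and oxytocin/ergometrine will proceed using a two-sided 95% CI". Non-inferiority is declared if that interval excludes the margin. No second, adjusted interval is given there.

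**The concern.** Two things do not line up.

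- **The interval level.** A two-sided 98% interval corresponds to a level of 0.02. The Bonferroni level that the article itself uses for three contrasts, 0.0167, corresponds to 98.33%.
- **The decision rule.** The two-tier scheme covers all three contrasts, but the analysis section turns the upper tier into a rule only for contrasts decided by a p value. Non-inferiority is decided by an interval, and the only interval named is the 95% one. A reader of that section cannot tell what would count as definitive evidence of non-inferiority.

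The article rests the case for preferring carbetocin to oxytocin/ergometrine on non-inferiority together with fewer side effects. What counts as definitive non-inferiority should therefore be unambiguous before the data are analysed.

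**Working it through.** **Inputs**
- Three primary contrasts; adjusted level 0.0167 (Sample size).
- Rates of additional uterotonic use: oxytocin/ergometrine 15.2%, carbetocin 11.5% (Table 1).
- n = 1904 per arm (Sample size).
- Margin 1%, read as 1 percentage point because the interval is for a difference in proportions (Non-inferiority comparison).
- Stated power: 95% with the 95% interval, 88% with the 98% interval (same subsection).

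**Step 1: the level**
- 1 − 0.05/3 = 0.98333, a two-sided 98.33% interval.
- Critical values: 1.960 (95%), 2.326 (98%), 2.394 (98.33%).

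**Step 2: the stated power from Table 1**

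Normal approximation with unpooled variance:
- SE = √[(0.152 × 0.848 + 0.115 × 0.885)/1904] = 0.01101.
- Power = Φ[(0.01 + 0.152 − 0.115)/SE − z] = Φ(4.270 − z).

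| Interval | z | Power from Table 1 | Stated |
|---|---|---|---|
| 95% | 1.960 | 99.0% | 95% |
| 98% | 2.326 | 97.4% | 88% |
| 98.33% | 2.394 | 97.0% | not stated |

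The stated figures do not reproduce. A pooled variance or a continuity correction moves the results by at most 0.4 points. The gap comes from the inputs, not from the interval level. For example, assumed rates of 15% and 12% would give 95.1%, 90.1% and 88.9% in the three rows. That discrepancy is a separate matter.

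**Step 3: the adjusted power implied by the stated 95%**

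This step needs no event rates. A power of 95% with a 95% interval implies a standardised distance of 1.960 + 1.645 = 3.605.
- At 98%: Φ(3.605 − 2.326) = 89.9%.
- At 98.33%: Φ(3.605 − 2.394) = 88.7%.

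The printed 88% matches neither exactly but lies nearer the 98.33% result.

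**Step 4: where the rule affects the conclusion**

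Non-inferiority needs the upper limit for carbetocin minus oxytocin/ergometrine to lie below +1 point. With SE = 1.10 points, the observed carbetocin advantage must exceed z × SE − 1:
- 95%: 1.960 × 1.1007 − 1 = 1.16 points.
- 98%: 2.326 × 1.1007 − 1 = 1.56 points.
- 98.33%: 2.394 × 1.1007 − 1 = 1.64 points.

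An observed advantage between about 1.16 and 1.64 points meets the rule in the analysis section but not the 0.0167 tier. Only between 1.56 and 1.64 points does the choice of 98% or 98.33% matter.

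**The case against.** The strongest reply has four parts.

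- **Rounding.** The neighbouring figures are whole percentages, and 98.33% rounds to 98%. The article never prints a level of 0.02, and Step 3 favours 98.33% slightly. This stands: a rounded label is the likelier explanation. It does not remove the need to print the exact level, since 0.0167 is given to three significant figures in the same subsection.
- **The 98% figure is not a decision rule.** It occurs only in a conditional statement about power. This also stands. A reader might infer that definitive non-inferiority would be claimed at a looser level than definitive superiority, or might add 0.0167 + 0.0167 + 0.02 and conclude that the allocated 0.05 is exceeded. The document does not support either inference, because the following paragraph sets 0.0167 for definitive evidence and nothing declares non-inferiority at 0.02.
- **Two tiers are deliberate.** The levels 0.05 and 0.0167 do not conflict; the superiority contrasts carry both. The 95% interval in the analysis section is the first tier, so combining it with the upper tier of the other two contrasts mixes tiers and describes no rule in the protocol.
- **Condensed text.** The analysis section is a summary and refers to a full statistical analysis plan that is not shown, and the sample-size section already gives the adjusted level. This lessens the point but does not remove it. The article does state the non-inferiority rule, and as stated the rule omits a tier that it spells out for the other two contrasts.

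**Conclusion.** The point holds as a minor wording correction to the decision threshold of a primary contrast. The 98% label is inexact for 0.05/3, and the analysis section does not carry the definitive tier into the non-inferiority rule. The protocol as a whole is not silent on the adjusted level for this contrast, and no inflated error rate follows from its text.

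The label alone is worth 0.4 points of power at the Table 1 rates (97.4% to 97.0%), or 1.2 points starting from the stated 95% power (89.9% to 88.7%). The missing tier has more substance, but only for the range of results found in Step 4. That range assumes a 1-point margin, 1904 per arm and the Table 1 standard error; it would shift somewhat with the rates actually observed.

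**What to change.** 1. In the Non-inferiority comparison subsection, replace the 98% interval by a two-sided 98.33% interval.
2. In the data analysis section, keep the two-sided 95% interval as the first tier. Add that definitive non-inferiority requires the two-sided 98.33% interval for the difference in proportions to lie on the correct side of the margin.
3. State the power at the 98.33% level and the inputs behind it: about 97.0% from the Table 1 rates, or about 88.7% if derived from the stated 95% power. Which of these applies depends on resolving the separate mismatch with Table 1.

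These are wording changes. They leave the sample size, data collection and conduct of the trial unchanged. Because recruitment is complete, they should be settled in the analysis plan before the arms are compared.

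### The three primary contrasts are judged at both an unadjusted 0.05 and a Bonferroni 0.0167, without saying which answers the primary aims; the first tier does not control the family-wise error

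*Protocol article*

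**What the plan says.** The primary aims are three contrasts on the need for additional uterotonic drugs: superiority of oxytocin/ergometrine over oxytocin, superiority of carbetocin over oxytocin, and non-inferiority of carbetocin to oxytocin/ergometrine.

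- Sample size, Non-inferiority comparison: alpha = 0.05 "will be used to determine statistical significance for all three contrasts, and additionally a threshold of" 0.0167 is kept for definitive evidence. This covers all three contrasts and is said to follow a regulatory guideline on multiplicity.
- Data analysis: a superiority contrast is significant if the effect is in the anticipated direction and the two-sided p value is below 0.05. Then: "Definitive statistical significance will be declared if the *p* value is below 0.0167". The "non-inferiority comparison between carbetocin and oxytocin/ergometrine" is decided on a two-sided 95% CI only; no second tier is given.
- Sample size, Superiority comparisons: power for oxytocin/ergometrine versus oxytocin is at least 88% at 0.05, and "The comparison would have a power of 80% for a Bonferroni-corrected level of nominal significance" of 0.0167.

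No order of testing, gate or step-down is stated. The omnibus chi-square test is planned but is not made a condition for the pairwise tests.

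**The concern.** A primary contrast with p between 0.0167 and 0.05 is significant but not definitive, and the article does not say whether the aim has then been met. The label is fixed in advance; its meaning for the trial's conclusion is not. That leaves room for selective emphasis in the report.

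The tier called statistical significance carries no adjustment across the three contrasts, so a reader who takes that label at face value accepts more error than a single 5% test implies. For non-inferiority, the two sections disagree on whether a definitive tier exists at all.

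**Working it through.** **Inputs.** 1904 per arm: "A complete sample of 5712 participants (1904 per arm) providing data for the primary outcome". Allocation: "Participants will be randomised to parallel arms in a 1:1:1 ratio". No allowance for drop-out: "therefore, the sample size has not been inflated". Table 1 rates: oxytocin 19.1%, oxytocin/ergometrine 15.2%, carbetocin 11.5%. Non-inferiority margin: 1 point. A two-sided 0.05 with a direction condition is 0.025 one-sided per contrast.

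**1. The plan's own power.** Power = Φ[(p₁ − p₂ − z·s₀)/s₁], with s₀ = √(2p̄(1 − p̄)/n) and s₁ = √((p₁(1 − p₁) + p₂(1 − p₂))/n). For 19.1% versus 15.2%, s₀ = 0.01222 and s₁ = 0.01220.

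- α = 0.05: (0.039 − 1.960 × 0.01222)/0.01220 = 1.234, so power is 89.1%.
- α = 0.0167: (0.039 − 2.393 × 0.01222)/0.01220 = 0.800, so power is 78.8%.

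At the rounded 19% and 15% the results are 90.8% and 81.4%. The stated 88% and 80% reproduce within about 2 points.

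**2. Error of each tier.** Simulation used 1904 per arm, a pooled z test for superiority and an unpooled z test against the 1-point margin for non-inferiority. All rules are directional, so the reference is 2.5% one-sided. The entries are the chance of at least one false claim.

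| True state | Unadjusted 0.05 | Bonferroni 0.0167 | Holm |
|---|---|---|---|
| Oxytocin 15%, oxytocin/ergometrine 15%, carbetocin 16% | 5.1% | 1.7% | 1.7% |
| All arms equal (15.2%) | 4.6% | 1.6% | 1.7% |
| Carbetocin = oxytocin, oxytocin/ergometrine 1 point better | 4.6% | 1.6% | 1.7% |

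The first row can be checked by hand. Two nulls lie on their boundary at about 2.5% each, and carbetocin versus oxytocin adds about 0.25%. The sum is 5.25%, and a small overlap brings it to 5.1%.

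**3. Trials between the tiers.** At Table 1 rates, oxytocin/ergometrine versus oxytocin is rejected in 89.2% of simulated trials at 0.05 and in 78.9% at 0.0167. The difference is 10.3%.

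**4. Power under Holm.** Holm compares the ordered two-sided p values with 0.05/3, 0.05/2 and 0.05, stopping at the first failure. At Table 1 rates:

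| Contrast | Unadjusted | Bonferroni | Holm |
|---|---|---|---|
| Oxytocin/ergometrine vs oxytocin | 89.2% | 78.9% | 89.2% |
| Carbetocin vs oxytocin | ~100% | ~100% | ~100% |
| Non-inferiority | 99.0% | 97.0% | 99.0% |
| All three | 88.2% | 75.9% | 88.2% |

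With carbetocin at 15.2%, equal to oxytocin/ergometrine, the two superiority contrasts have about 89% power unadjusted, 79% under Bonferroni and 82–83% under Holm. With carbetocin 1 point worse (16.2%), carbetocin versus oxytocin has 65.1% unadjusted, 48.2% under Bonferroni and 53.1% under Holm.

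**Side note.** The stated non-inferiority power (95%, and 88% with a 98% CI) does not reproduce at Table 1 rates with a 1-point margin: I get 99.0% and 97.4%. To test whether this matters, the carbetocin rate was set to 12.25%, where unadjusted and Bonferroni non-inferiority power are 94.4% and 87.6%, close to the stated pair. Holm then gives 94.3%, and 89.1% for oxytocin/ergometrine versus oxytocin, so the comparison of rules does not depend on it.

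**The case against.** The strongest reply is that strict control is already present. The definitive tier is Bonferroni over three contrasts, its error is 1.6–1.7%, and power is disclosed at both levels. The superiority labels are prespecified: p = 0.03 in the anticipated direction is significant and not definitive, with no discretion. All of this stands. A reader might infer that the trial has no multiplicity control, or that investigators may pick a verdict after seeing the data; the text supports neither. What remains is that the article does not say which tier answers the aims.

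A reader might also infer inflation near 1 − 0.95³ = 14.3%. That counts three independent two-sided tests. The plan has two directional superiority tests and one test against a margin, and the three nulls cannot all sit on their boundaries together. The inflation is about two-fold.

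How far to adjust across three distinct drug questions is debated, and Bonferroni and Holm both control the error. Choosing Holm is therefore a matter of efficiency, but it is not a trade-off against Bonferroni, because Holm rejects whatever Bonferroni rejects.

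Finally, the full analysis plan, which is not shown, might make the omnibus test a gate. In the first two null states above (run with oxytocin at 15.2%), a gate would lower the error to 1.9% and 2.1%. Its absence from the article is not held against the plan; the two-tier rule and the disagreement on non-inferiority are stated in the article itself.

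**Conclusion.** The point holds in limited form. The 0.05 tier allows about a 5.1% chance of at least one false directional claim, twice the 2.5% one-sided level; the 0.0167 tier does control it. The article does not name the tier that settles the primary aims, which at Table 1 rates would matter in about one trial in ten for oxytocin/ergometrine versus oxytocin. The two sections also conflict on non-inferiority.

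These sizes assume 1904 analysed per arm and normal-approximation tests. The claim that Holm loses essentially nothing against unadjusted 0.05 is tied to the Table 1 rates, which the article itself says may be imprecise. A reader might infer that Holm keeps the planned 0.05-level power in general. It does not: with carbetocin equal to oxytocin/ergometrine, superiority power falls about 7 points, below the stated 88%. The general statement is that Holm is never less powerful than the planned Bonferroni tier.

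**What to change.** Name one confirmatory rule: Holm's step-down procedure over the three primary contrasts at overall two-sided 0.05, directional, with the non-inferiority p value taken against the 1-point margin. It replaces the Bonferroni tier. Label the unadjusted 0.05 results and the 95% CIs as nominal or descriptive, and drop the two grades of significance. Reconcile the Non-inferiority comparison and Data analysis sections so that non-inferiority is decided by this same rule.

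The cost is wording in the protocol and analysis plan; no participants or data are added. Recruitment is complete and the DMC has reviewed the primary outcome at half recruitment, so the change should be dated and made by people without access to comparative results. The price is the power loss shown above when carbetocin is no better than oxytocin/ergometrine. A lone contrast with p between 0.0167 and 0.05, with no other rejection, would no longer be called significant.
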